5.0 STUDY DESIGN

**5.1 Study design**

A multicenter, cluster randomized clinical trial at the level of the General Practitioner (GP) comparing a pro-active, multi-component (multidisciplinary and multidimensional) intervention, coordinated by a Health Care Nurse (HCN) with care as usual.

##### Figure 1 flow chart of patient selection and randomisation (next page)

##### 5.2 Duration of the study and follow-up

##### The study will start September 1, 2010. The screening phase will take 6 months and the following intervention 12 months (including all intended 7 follow-up contacts). After 12 months, all elderly people in both arms of the trial will receive a postal questionnaire to score the modified Katz ADL index. To assess long-term effects, a similar postal questionnaire will be send after 18 and 24 months. The final analysis will be reported around September 2013.

**Total population ≥70 yrs**

**n=8220**

**Baseline measurement**

**n=5670**

**Increased risk: ±50%**

**Invitation for CGA**

**n=1418 (100%)**

**CGA**

**n=1134 (80%)**

**Intervention: 10/11 GP practices; N≈2835**

**Exclusion (6%, n=658):**

- Restricted life expectancy

- Dementia

- Planning to move

- Unable to speak Dutch

**Non respondents**

**(25%, n=1891)**

Declining to participate or unable to contact

**Follow-up measurements**

**Katz-ADL/ALDS**

**Hospital/nursing home admissions**

**Quality of Life**

(6, 12, 18, 24 months)

**Eligible elderly people receiving ISAR-PC**

**n=7562**

**Control: 10/11 GP practices;**

**N≈2835**

**Non- respondents**

**(20%, n=284/1418)**

**No care/tr. plan**

**(25%, n=284/1134)**

**Care/treatment**

**7 follow-up contacts**

**n=850 (60%)**

**Intervention:**

**CGA and care/treatment starting with ±50% of total population in intervention practices**

6. TREATMENT OF SUBJECTS

I SCREENING OF THE ELDERLY POPULATION

First, all eligible elderly people who are registered with their GP will be sent a postal questionnaire, the Identification of Seniors at Risk in Primary Care (ISAR-PC), containing 4 yes/no questions. This instrument originally consisted of 6 yes/no questions, i.e. on problems with activities of daily life, memory, or recent falls. It was developed to predict the risk for functional loss of patients attending the Accident and Emergency Room (McCusker, 1999) and modified for the primary care setting during a pilot phase of the current study.

II INTERVENTION: THE CARE COORDINATION PROGRAMME

The core of the intervention (health care coordination) concerns the activities of the health care nurse (HCN), that has been specifically designed with/for elderly people. Integrating components from disease management and case management, the HCN offers an evidence based care and treatment plan, tailored to each individual patient.

The primary care geriatric team (HCN and the general practitioner (GP)) will bear active responsibility for implementing the health care coordination. The practice nurse is an experienced, registered nurse (5th expertise level) with a special focus on elderly care.

The health care coordination programme consists of two phases:

1) Postal screening for an increased risk of functional decline (ISAR-PC).

2a) An increased ISAR-PC score (≥2) is followd by a comprehensive geriatric assessment (CGA) focussing on over 30 geriatric problems that are most prevalent in primary health care (measured in 4 domains: physical, functional, mental, and social functioning).

2b) After the CGA an individual care and treatment plan aims for the prevention of (further) functional decline. For the systematic identification of geriatric problems and proposition of subsequent interventions and integrated protocol is used, referred to as ‘the toolkit’. It was developed during the Defence-study (www.defencestudy.nl) and further extended and modified during the pilot phase of this study (see also Appendix 2 and 3). The toolkit contains internationally validated instruments to identify geriatric problems (such as the Mini Mental State Examination and the Geriatric Depression Scale; see Appendix 2 for overview). The interventions proposed in the toolkit are evidence-based or based on current best practices. The intervention will be worked out in detail and implemented for each problem field. The provision of information, support, advice and/or instructions may be related to medication adherence, fall prevention, etc. but also to the consultation of other health care professionals. For example, in case of poly-pharmacy, the pharmacist may be involved; when the fall-risk appears to be increased an ergotherapist will be asked to scrutinize the home for accident-prone elements, and in case of loneliness or lack of meaningful activities, contact with a social worker can be instigated to explore the opportunities for improved social participation. A consultation with a nursing home physician or a visit to the geriatric outpatient clinic can also be part of this process. The care and treatment plan will always be talked through with the patient (and/or informal caregiver if appropriate) first to explore his/her willingness to participate in any form of improvement plan, after which advice from the GP will be obtained.

7. METHODS

**7.1 Study parameters/endpoints**

The primary outcome measure is the level of (instrumental) activities of daily living (baseline-12 months), measured with the modified Katz ADL index (15 items).

### 7.1.1 Main study parameter/endpoint

See 7.1

### 7.1.2 Secondary study parameters/endpoints

Secondary outcomes will be differences in hospital admissions, nursing home admissions and disability (measured with the AMC Linear Disability Scale, ALDS) after 12 months. Likewise, differences in quality of life will be studied (EQ-5D, RAND 36) as well as met and unmet care needs (CANE) (see also ‘minimal data set’: [www.nationaal](http://www.nationaal/) programmaouderenzorg.nl/toolkit) [NB The ALDS is a generic and validated continuous scale that has scores ranging from 0 to 100, with a lower score expressing more impairments in daily functioning.]

### 7.1.3 Other study parameters

The presence of geriatric conditions that are assessed will be registered as co-variates in the prediction model (see appendix 2 for the exact content)

Process evaluation

Apart from the primary and secondary outcomes, supplementary qualitative and semi-qualitative data will be collected to provide insight at the professional and the network level into the practicability and feasibility of the intervention. Qualitative data will also be analysed in search of factors that could enable or inhibit the future implementation of the care programme. Further specifications follow below.

1] Professional/network level

(a) The effects of the experiment on the feasibility and continuity of the requested and offered care, on professional expertise, on experienced work pressure, on satisfaction about the organisation and on the content of the primary and secondary care that is provided. In addition, the frequency will be registered of specific requests resulting in consultation of the geriatrics adviser, the nurses working in home care, the paramedics working at the primary care level, and services at the secondary and tertiary care levels.

(b) Content of the intervention: a process evaluation will be conducted into the rate of fully implemented intervention plans. In addition, the four distinct components (physical, functional , mental, and social) of the intervention and follow-up will be evaluated separately.

2] Factors facilitating or inhibiting the implementation of the care programme

Examples of questions that will be addressed here are:

- Are all elderly from the target group being screened for their risk profile?
- Are the geriatric problems of all elderly with a positive screening (i.e. an increased risk of functional decline) being described according to the agreed system?
- Do the health care nurses (HCN) visit the elderly person at home or are participants seen in the GP office? What are the constraining factors in either routes? Is there a perceived added benefit to home visits?
- Does the HCN contact the caregivers/family?

- Do the contacts with HCN/(para)medical personnel take place within the indicated time frame?

- Do elderly persons feel that their care needs are addressed? Where is room for improvement?
- Is the composition of the primary care team around the patient appropriate, is a specific player missing, or are there perhaps too many players?

**7.2 Randomisation, blinding and treatment allocation**

This is an cluster randomized controlled trial in the Netherlands, comparing regular care as control condition with a nurse led, multi-component intervention directed at geriatric problems as the experimental condition. Whereas randomization takes place at GP level, interventions take place at the individual level on the basis of identified geriatric problems. A pre-randomization procedure will be followed to allow for the allocation of a practice nurse to the intervention practices. This requires a few months of preparation, during which the nurses will take part in a specialized elderly training program and logistical preparations will be made regarding necessary consultation rooms and equipments. The randomisation procedure will be website-based, using permuted blocks (maximum block size of 4) and stratified by median number of patients (1) and social status score (2) in each GP practice.

Patients in practices randomized to the control condition receive care as usual according to the current guidelines for Dutch general practice. At baseline, all patients will receive a postal questionnaire to assess their overall risk on functional loss. In the intervention practices, patients with increased risk profiles will be asked to participate in further geriatric assessments and follow-up through an integrated care and treatment plan.

In the control condition, the results of the postal questionnaires on patients with increased geriatric risk profiles will be made available to the GPs at the end of the intervention, to minimize contamination effects. Patients without increased risk in the in the intervention practices and all patients in the control practices will be blinded to the intervention through the use of a postponed informed consent procedure, described by Boter et al (2005). See also Figure 1 (5.1 ‘Study design’). This informed consent procedure is chosen to minimize Hawthorne effects among the patients who are not invited to attend the geriatric assessments and its successive follow-up. In the information letter to the patient, the purpose of the study will be explained, without specifically mentioning the intervention by the practice nurse. Targeted patients in the intervention group are further informed about the care coordination. After termination of the study, patients in both study groups will be informed about the research question and interventions that took place (*single-delayed consent design,* Schellings 2005).

The project will include the equivalent of 21 GP practices in the region of Alkmaar and will be randomised in a ratio of 1:1. Randomization is performed by the AMC Clinical Research Unit (CRU).

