**Nature and extent of the burden and risks associated with participation, benefit and group relatedness**

All elderly people with increased risk for functional loss will be subjected to a comprehensive geriatric assessment (appendix 2) that will approximately last one hour and is expected to take place in the GPs' surgery or at home (if the patient is not able to come to the GP practice). The identified problems are discussed with the GP and the patient and are translated into a care and treatment plan. Examples of potential interventions are consultations of an ergotherapist or physiotherapist for elderly people with increased fall-risk and/or impairments in their mobility. The nurses aim for 7 follow-up contacts within one year, through office consultations, home visits or telephone contact if warranted. The practice nurse will work in close collaboration with the GP, evaluating the care and treatment plans in the course of the follow-up, while looking out for emerging new problems over time.

Participants in the control group may not benefit from filling out the questionnaires, although their response will be analyzed over time and will be made available to their GP toward the end of the study, thus yielding potential new (or existing) problems that can be (further) addressed.

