11.0 ADMINISTRATIVE ASPECTS AND PUBLICATION

**11.1 Handling and storage of data and documents**

The data will be handled by the investigators of the study ([name], [name], [name], [name]). They will have access to the source data. One of the project leaders (SR) will have access to the randomization code. Data will be entered according to AMC Good Clinical Practice Guidelines with a number and fictional initials for each patient and a double data entry process. The communication data will be erased within six month after the termination of the study.

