**11.4 End of study report**

The PI will notify the accredited METC and the competent authority of the end of the study within a period of 90 days. The end of the study is defined as the last patient’s follow up after 12 months is completed.

In case the study is ended prematurely, the PI will notify the accredited METC and the competent authority within 15 days, including the reasons for the premature termination.

Within one year after the end of the study, the PI will submit a final study report with the results of the study, including any publications/abstracts of the study, to the accredited METC and the Competent Authority.

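### The study is defined to end at 12 months but outcomes run to 24, so patient disclosure, data erasure and control-GP feedback can precede the long-term questionnaires

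*Protocol*

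**What the plan says.** Section 5.2 gives a start of 1 September 2010, six months of screening, twelve months of intervention and a final analysis around September 2013. It adds: "To assess long-term effects, a similar postal questionnaire will be send after 18 and 24 months". Figure 1 and the table in section 7.3 show questionnaires at 6, 12, 18 and 24 months, and the table marks them for both arms.

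Section 11.4 states: "The end of the study is defined as the last patient’s follow up after 12 months is completed". It asks for the final study report within one year of that date.

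Three provisions depend on when the intervention or the study ends:

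- **Feedback to control GPs.** Under section 7.2, results for control patients at raised risk "will be made available to the GPs at the end of the intervention, to minimize contamination effects". The Summary says that control responses "will be made available to their GP toward the end of the study, thus yielding potential new (or existing) problems that can be (further) addressed".
- **Disclosure to patients.** Section 7.2: "After termination of the study, patients in both study groups will be informed about the research question and interventions that took place".
- **Erasure.** Section 11.1: "The communication data will be erased within six month after the termination of the study".

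No section holds any of these back until the 24-month questionnaires are in, and section 9 does not qualify the long-term comparison. The primary outcome (7.1) runs from baseline to 12 months, and section 7.1.2 places the secondary outcomes after 12 months.

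**The concern.** The protocol takes care to keep control care and patient reporting undisturbed. It withholds risk results from control GPs to limit contamination, and it postpones full information to limit Hawthorne effects on a self-completed postal questionnaire. Both safeguards are tied to the end of the intervention or of the study, not to the end of outcome collection. Read with section 11.4, they may lapse halfway through the planned 24 months.

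What is at stake is the long-term comparison. A null result at 24 months could mean that the effect faded, or that control patients received extra attention once their GPs had the results. Answers given after patients learn the purpose of the trial may differ from those given before. If contact details have been erased, the last mailing has no evident route from the study team.

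**Working it through.** The point is one of timing, so there is no plan figure to reproduce.

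**Inputs.** Start September 2010 (5.2); recruitment about 6 months, with the last practices ending 6 months after the first (7.3 footnote); questionnaires at 6, 12, 18 and 24 months (7.3); end of study at the last patient's 12 months (11.4); erasure within 6 months of termination (11.1).

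**Calendar.** Date = September 2010 + recruitment offset (0 or 6 months) + questionnaire month.

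| Event | First practices | Last practices |
|---|---|---|
| Baseline | Sept 2010 | March 2011 |
| Month 12 | Sept 2011 | March 2012 |
| Month 18 | March 2012 | Sept 2012 |
| Month 24 | Sept 2012 | March 2013 |

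- End of study under 11.4: September 2010 + 6 + 12 months = about March 2012.
- Latest erasure date, if termination means that date: March 2012 + 6 months = about September 2012.

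**Comparison.** Every month-18 questionnaire falls at or after the 11.4 end of study. Every month-24 questionnaire falls at or after the latest erasure date.

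**Check against the reporting dates.** Section 11.4 would require the final report by March 2012 + 12 months = about March 2013. That is when the last 24-month questionnaires fall due, and about six months before the final analysis planned in 5.2. If the study instead ended at the last 24-month questionnaire (about March 2013), the erasure limit would be about September 2013, in line with 5.2. The 12-month definition in 11.4 therefore looks like the text that is out of step.

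**GP feedback.** This limb does not depend on 11.4. If results are released practice by practice at month 12, 12 of the 24 months follow release for everyone. If there is one trial-wide release in about March 2012, the first practices are at month 18 (24 − 18 = 6 months remain) and the last at month 12 (24 − 12 = 12 months remain). In both cases the 18- and 24-month questionnaires fall at or after release.

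**Upper bound on exposure.** Control practices hold about 2,835 respondents. If half are at raised risk, as Figure 1 states for the trial, 2,835 × 0.5 ≈ 1,418. This assumes the same share in control practices and ignores deaths and non-response.

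**Illustration of dilution (losses assumed, not in the protocol).** Take 850 per arm with complete data, design effect 1.08, d = 0.20 and two-sided alpha 0.01 (4.4). Reading 850 as per arm follows Figure 1, which places it in the intervention arm. Then n_eff = 850/1.08 = 787, and power = Φ(d × √(787/2) − 2.576).

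| Contrast lost | d | Power |
|---|---|---|
| 0% | 0.20 | 92% |
| 10% | 0.18 | 84% |
| 20% | 0.16 | 73% |
| 30% | 0.14 | 58% |
| 50% | 0.10 | 28% |

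The trial is not powered on the later time points. The table shows only how sensitive such a comparison would be.

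**The case against.** The best defence is that section 11.4 concerns notification of the ethics committee, and that sections 7.2 and 11.1 speak of termination without referring to it. Mailings to 24 months and an analysis in September 2013 suggest that the investigators mean termination to follow the last questionnaire. On that reading disclosure and erasure do no harm. This stands as far as it goes: equating the two terms is an inference. But 11.4 holds the only definition of the end of study in the protocol, so someone following the text could act on it.

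Several stronger readings are tempting but not supported:

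- **That patients will be unblinded before month 24.** Section 7.2 sets no deadline for disclosure. It permits early disclosure but does not require it.
- **That the 24-month data cannot be collected.** Communication data is not defined, and GP practices hold their own patient records, so another postal route may exist.
- **That the later comparison is contaminated.** Control practices receive questionnaire results only. They get no geriatric assessment, trained nurse, care plan or seven contacts. What their GPs would do is unknown, and the Summary presents the feedback as a possible benefit to control patients. Yet section 7.2 itself treats release as a contamination risk, and the Summary expects problems to be acted on.
- **That the Summary and section 7.2 plainly conflict on release.** Under 11.4 the two times largely coincide. They separate only if the study ends at 24 months, which is why they need aligning once 11.4 is corrected.
- **That the later comparison stops being randomised.** Under intention to treat it stays randomised. Only the comparator changes.

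One may also say that 18 and 24 months merely test whether an effect persists. That is a fair aim, but it needs control care to remain as it was.

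**Conclusion.** The protocol contradicts itself on when the study ends: about March 2012 under section 11.4, against outcome collection to about March 2013 under sections 5.2 and 7.3.

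If termination carries the 11.4 meaning, patients may be told of the question and intervention before months 18 and 24. Communication data, if these are contact details, must also be gone by about September 2012, at or before all the 24-month mailings. Both consequences rest on that reading, and the second also on the meaning of the term.

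Independently, feedback to control GPs at the end of the intervention comes before the long-term questionnaires. The 18- and 24-month comparison is therefore open to contamination, probably toward no difference. Its size is unknown, and at most about 1,418 at-risk controls are exposed.

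The 12-month primary and secondary outcomes and the sample size are not affected. The point deserves correction because it is cheap and protects a stated aim, but it does not threaten the main result.

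**What to change.** 1. In section 11.4, define the end of study as completion of the last patient's 24-month questionnaire.
2. In sections 7.2 and 11.1, tie patient disclosure and erasure of communication data to that date, and say what communication data covers.
3. State one release time for control-practice results in both the Summary and section 7.2. There are two options:
   - release after the last 24-month questionnaire; or
   - keep earlier feedback, and state in section 9 that the 18- and 24-month comparison remains randomised but is against usual care plus GP feedback, and is exploratory.

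This is a small text amendment. Contact data would be kept about a year longer (latest erasure about September 2013 instead of September 2012). Patients would be told later, and under the first option control GPs would also receive the results later.

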**7.3 Study procedures**

| **Measures** | **Intervention group** | **Control group** |
| --- | --- | --- |
| **<4 wks,** Extractions from electronic medical records (in Dutch: Huisarts Informatie Systeem, HIS) by GP of all patients aged 70 and over.  Screening for eligibility by GP (inclusion criteria). | **X** | **X** |
| **<2 wks** Pre-randomisation at the level of GP practices | **X** | **X** |
| **Start of study (Sept. 2010):**  Postal questionnaires (i.e. ISAR-PC, Katz-ADL, MDS), along with study information and postponed informed consent | **X** | **X** |
| **6 wks**  -Comprehensive Geriatric Assessment: (CGA; Appendix 2).  -Integrated care and treatment plan, discussed with both patient and GP  -Start of implementation care and treatment plan; follow-up contact with practice nurse (and other care givers if indicated) is planned | **X** |  |
| **6 wks – 12 months***  Follow-up contacts (7) by nurse to monitor the care and treatment plan | **X** |  |
| **6-12-18-24 months**  Postal questionnaires containing KATZ-(I)ADL, ALDS (T0/T12) and MDS. | **X** | **X** |

*** Total recruitment period will take around 6 months; therefore, the last GP practices included will end 6 months later than the first.**

